### Statistical analysis

**Research hypothesis**

This trial is designed to investigate the superiority of onabotulinumtoxinA compared to placebo when injected into the SPG using the MultiGuide® device with respect to the number of moderate to severe headache days:
•The null hypothesis is that the average change from baseline in the number of moderate to severe headache days during weeks 5-8 post-injection does not differ between participants receiving onabotulinumtoxinA or placebo.•The alternative hypothesis is that the average change from baseline in the number of moderate to severe headache days during weeks 5-8 post-injection differs between participants receiving onabotulinumtoxinA or placebo.

**Sample size**

The MiBlock trial has a confirmatory statistical strategy that pre-specifies just one single hypothesis related to the primary endpoint. To that end, the sample size was calculated by a professional, independent biostatistician based on the data from the pilot study.
^
18
^ The standard deviation (SD) for the change in number of headache days per week between baseline and week 5 – 8 was 7. To detect a difference of 3.5 moderate to severe headache days per month between active and placebo groups in weeks 5 – 8, provided 80% power to reject the null hypothesis at 5% level nominal of significance and assuming a drop-out rate of 25%, a total of 170 patients will be randomised to treatment in this study. The chosen effect size was informed by results from the pilot study and by a clinical assessment of what would constitute a clinically meaningful benefit, particularly in light of the invasive nature of the treatment procedure.

**Subject adherence, protocol deviations and violations**

The definition of protocol deviation and violation is based on the following statement
^
31
^ and should in this study cover all incidences of participant non-adherence to study procedures after enrolment (ie. post-randomisation). Protocol violations in this study are headache diary nonadherence defined as <90% adherence and/or alterations in headache preventive treatment during trial participation. Electronic headache diary adherence will be calculated at 4-week (28 days) intervals. Protocol violators are excluded from the per protocol analysis.

### Statistical analysis

The main analysis is planned when all participants have concluded the 12-week follow-up after the injection and the database has been locked. All statistical analyses are pre-planned and will be described in a SAP finalised prior to data lock. The SAP will also include a preplanned order for data analysis, as well as the results table templates for the blinded analysis. The order of data analysis is defined a priori in order to ensure that the main efficacy analyses are completed without the risk of unblinding which may occur when analysing the safety data.

The full analysis set (FAS) will include all randomised participants who received the injection. To adhere to the intention-to-treat ideal for the FAS population, participants that undergo unsuccessful injections (i.e. Investigative medicinal product (IMP) not administered bilaterally or unilaterally) are included in the FAS.

The FAS will be used for all efficacy analyses. Briefly, for the primary outcome, a mixed logistic regression model will be used to estimate the difference in the change from baseline in mean monthly headache days between the treatment and placebo group. The model will include the presence or absence of headache on each day with recorded information from baseline until 12 weeks after the injection as a dependent binary variable, treatment allocation, time-period (baseline, week 1-4, week 5-8 and week 9-12) and an interaction term between treatment allocation and post-injections time-periods are included as categorical fixed effects, and with participant ID as a random effect. Site of inclusion will also be assessed as a potential random effect prior to unblinding of the statistician to treatment allocation. All available data will be included in this analysis, regardless of proportion of eDiary days completed. The model works under the assumption that data are missing at random. No formal missing-not-at-random analysis are preplanned.

The analysis of secondary outcomes will use the same strategy, although using mixed linear regression models for continuous outcomes. Additionally, sensitivity analyses for the primary and secondary outcomes will be performed, which will include restriction analysis to the subgroup of participants with technically successful bilateral injections and the per-protocol
set. Analysis across all three postintervention 28 day periods will be performed, to allow evaluation of temporal patterns of treatment response.

For responder endpoints, responder status is defined based on the percentage change in the number of moderate to severe headache days, comparing each 28-day post-intervention period with the 28-day baseline period. To reduce the risk of uncertainty or misclassification of responder status due to incomplete data, responder endpoints will be calculated only for participants who have completed at least 90% of daily headache diary entries in both 28-day periods used for the respective comparisons.

Prespecified subgroup analyses will be conducted for each of the following baseline factors: sex, baseline medication overuse, patient-reported accompanying cranial autonomic symptoms during migraine attacks, and concomitant use of preventive treatments targeting the CGRP system.

A prespecified assessment of the success of the double blinding is included in the SAP and will be included in the statistical analysis report. The assessment will use the blinding index proposed by Bang et al.
^
32
^ In addition, the blinding index proposed by James et al.
^
33
^ will be calculated, and the results will be compared as recommended by Bang et al.
^
32
^

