### Primary efficacy endpoint

The primary efficacy endpoint variable is moderate and severe headache days, defined according to the guidelines of the International Headache Society.
^
20
^ Data capture is done prospectively as a patient-reported outcome in a study electronic headache Diary (eDiary). In the context of this study, a moderate or severe headache day is defined as a headache day with a recorded maximum pain intensity of ≥4 that lasts at least 4 hours or a day with a headache of any intensity which prompted the use of acute rescue medication. Rescue medications are defined as simple analgesics, triptans and opioids.

The primary efficacy endpoint is the change from the baseline in the number of moderate to severe headache days during weeks 5 to 8 following the intervention. The treatment effect will be assessed by comparing the average change in the treatment group to that in the placebo group. Post-injection weeks 5-8 are selected based on pilot study efficacy data suggesting that the frequency reduction the trial is designed to evaluate, reaches a plateau in this four-week period.
^
18,
19,
21
^

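### The primary model is described with headache yes/no as its outcome, without the moderate-to-severe qualifier that defines the primary endpoint; the description should be reconciled with the endpoint

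*Protocol article*

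**What the plan says.** **Endpoint.** The protocol article's section on the primary efficacy endpoint states: "The primary efficacy endpoint is the change from the baseline in the number of moderate to severe headache days during weeks 5 to 8". A day can qualify in two ways. The first rests on intensity and duration: "headache day with a recorded maximum pain intensity of ≥4 that lasts at least 4 hours". The second rests on treatment, whatever the pain level: "a day with a headache of any intensity which prompted the use of acute rescue medication".

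**Hypothesis and target.** The Research hypothesis section uses the same outcome: "The null hypothesis is that the average change from baseline in the number of moderate to severe headache days during weeks 5-8" is equal in the two arms. The Sample size section sets the target difference at 3.5 moderate-to-severe headache days per month.

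**Model.** The later of the two sections headed Statistical analysis introduces the analysis thus: "Briefly, for the primary outcome, a mixed logistic regression model will be used". The model's purpose is to "estimate the difference in the change from baseline in mean monthly headache days between the treatment and placebo group". Its daily binary outcome follows: "The model will include the presence or absence of headache on each day with recorded information from baseline until 12 weeks after the injection". Neither the outcome nor the estimated quantity mentions intensity, duration or rescue medication.

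**The concern.** The endpoint and the modelled variable, as worded, are two different daily indicators. A day with a mild or short headache and no rescue medication scores 1 on headache yes/no and 0 on the endpoint definition.

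The distinction exists in the data. Under Data collection, the eDiary first asks whether there was a headache. Only if there was does it ask about maximum intensity, duration at intensity 4 or more, and abortive medication. The phrase used for the model therefore matches the opening eDiary item, and a programmer could follow the text exactly and analyse a variable that is not the primary endpoint.

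At stake is the match between the trial's one confirmatory test and its one stated hypothesis. If treatment turned some moderate or severe days into mild untreated days, the endpoint would register that benefit and headache yes/no would not.

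**Working it through.** **1. The passages side by side**

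| Place in the protocol article | Outcome named |
|---|---|
| Primary efficacy endpoint | moderate-to-severe headache days |
| Research hypothesis (null and alternative) | moderate-to-severe headache days |
| Sample size, target difference | moderate-to-severe headache days |
| Sample size, SD of change | headache days, no qualifier |
| Statistical analysis, model outcome | headache present or absent, no qualifier |
| Statistical analysis, estimated quantity | monthly headache days, no qualifier |
| Statistical analysis, responders | moderate-to-severe headache days |
| Secondary efficacy endpoints | headache-free days, exploratory only |

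The qualifier is missing from both descriptions of the primary model and returns for responders in the same section. It is also missing once in the sample-size text, which shows that the article does use the bare term loosely.

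**2. What the literal reading would do.** Take a hypothetical participant with headache on all 28 days of both periods, all 28 being endpoint days at baseline. If half became mild and untreated, the endpoint would fall by 14 days and headache yes/no by 0.

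**3. The plan's own sample size.** Inputs from the Sample size section: difference 3.5, SD 7, power 80%, 5% level, 25% drop-out, total 170. Allocation is 1:1, and the alternative hypothesis is two-sided.

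- Normal approximation: n per arm = 2 × (1.960 + 0.842)² × (7/3.5)² = 62.8, so 63. The total is 126, and 126/0.75 = 168.
- t-test: 64 per arm, total 128, and 128/0.75 = 170.7.

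Both agree with 170. This requires SD 7 to be per 28 days. The section says per week; four times that, SD 28 per 28 days, would need 1005 per arm. That is a separate wording matter.

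The calculation is already for moderate-to-severe days, so correcting the model's outcome does not change N.

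**4. Power under the literal reading (assumed range).** The article gives no effect or SD for days with any headache. Let f be the share of the 3.5 averted endpoint days that become headache-free, the rest becoming headache days that do not meet the endpoint definition. The effect on headache yes/no is then 3.5 × f. Evaluable patients: 170 × 0.75 = 127.5, or 63.75 per arm.

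Power ≈ Φ( (3.5 × f / SD) × √(63.75/2) − 1.960 )

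For f = 0.5 and SD 7: 0.25 × 5.646 − 1.960 = −0.549, and Φ(−0.549) = 0.29.

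| f | Effect (days) | SD 7 | SD 6 | SD 5 |
|---|---|---|---|---|
| 1.00 | 3.500 | 81% | 91% | 98% |
| 0.75 | 2.625 | 56% | 70% | 84% |
| 0.50 | 1.750 | 29% | 38% | 51% |
| 0.25 | 0.875 | 11% | 13% | 17% |

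This compares two means, as the sample-size calculation appears to do. The planned mixed logistic model would give somewhat different figures, so the table is indicative only.

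**The case against.** The strongest reply is that this is shorthand. The model sentence presents itself as a brief account of the analysis for the primary outcome, and that outcome is fully defined earlier. The sample-size text drops the same qualifier for the SD and restores it for the target difference. The full specification is left to an SAP that is not shown. This stands as far as it goes: shorthand is plausible, and the article never refers to any headache as the outcome. It does not remove the need for correction. The article does not leave the dependent variable to the SAP; it names one, and the one named differs from the endpoint.

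A reader might infer three stronger points that the article does not support.

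- *That the analysis is less sensitive.* No effect or SD is given for days with any headache. A smaller SD could offset a smaller effect: SD 5 with f = 0.75 gives 84%. The two indicators may also be close, because any headache treated with rescue medication is an endpoint day and abortive drugs are unrestricted apart from opioids.
- *That many participants are at a ceiling.* Eligibility requires at least 15 headache days a month, about half of all days. No baseline distribution is given.
- *That there are two competing primary outcomes, open to choice after the data are seen.* The Sample size section commits to a single hypothesis on the primary endpoint. The article also plans an SAP finalised before data lock, result table templates, a fixed order of analysis and coded treatment groups.

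**Conclusion.** The inconsistency is real: the dependent variable and the estimated quantity given for the primary model do not carry the qualifier that defines the endpoint, the hypotheses and the target difference. Whether the planned analysis itself is wrong cannot be told from the article. If the wording is shorthand, only the description needs correcting. If it is literal, the confirmatory test would not address the stated hypothesis.

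The sample size stands under either reading. The loss of power is a conditional risk of the literal reading. Over the range examined, power runs from 98% down to 11%, and where it falls depends wholly on the assumed share of averted days that become headache-free and on an assumed SD for a variable the article does not describe. No single figure should be quoted as the expected loss. The case for correction rests on matching the one confirmatory test to its hypothesis.

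**What to change.** In the model description, and in the SAP and dataset specification if they use the same wording, state that:

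- the dependent variable is a daily yes/no indicator of a moderate-to-severe headache day, by the definition in the section on the primary efficacy endpoint;
- the estimand is the between-group difference in change from baseline in the number of such days per 28 days, at weeks 5-8;
- any analysis of days with any headache is separate and non-confirmatory.

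The cost is about one sentence in each document. No new data are needed, because the eDiary already records intensity, duration and abortive medication, and N is unchanged. The correction should be in place before data lock. If the SAP already defines the variable this way, aligning the article's wording with it is enough.

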**Figure 3. f3:**
[figure not shown]
Illustration of study procedures. **A.** The study includes participants at 4 sites, but injections sites are Trondheim and Oslo only. Injections are done in an office-based setting. A preplanned injection trajectory with a percutaneous access and real time navigation guides the injection.
**B.** Illustration of study progression for each participant. A screening visit followed by a 28-day minimum baseline period during which MR and CT scans are acquired. Follow rescreening, a single-session bilateral injection is performed, and a 12-week follow up initiated. Only AE occurring during injection or the follow up period (i.e. treatment emergent) are registered. Created by [name]. Printed with permission from © [name] @ScienceShaped.

Study participation is commenced by an inclusion visit followed by a baseline period of at least 28 days. Participants are instructed to keep a daily electronic headache diary (eDiary) for the entire duration of the study. At visit 2, prior to randomisation, a formal re-evaluation of study eligibility including a review of eDiary adherence and headache frequency, is performed. Participants assessed ineligible up to or at this point, are considered screening failures and excluded from the study. Treatment allocation follows a 1:1 ratio, with a computer-generated randomisation scheme applying block randomisation with randomly selected block sizes. CT and MR scans of the region of interest are performed prior to the injection procedure to allow trajectory planning and a navigation-guided injection. The follow-up period of 12 weeks ends with a final visit, which concludes study participation. At the end of this visit, participants and investigator are asked to assess blinding.

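### The primary model fits a free treatment difference at the pre-randomisation baseline, so it behaves as an unadjusted change-score comparison and may give up precision that the baseline diary could supply

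*Protocol article*

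**What the plan says.** In the protocol article, Methods, Statistical analysis, the plan is that "a mixed logistic regression model will be used to estimate the difference in the change from baseline in mean monthly headache days". The outcome is a daily yes/no record from baseline to week 12. The listed fixed effects are "treatment allocation, time-period (baseline, week 1-4, week 5-8 and week 9-12) and an interaction term between treatment allocation and post-injections time-periods". Participant is the one random effect named, with site still to be considered. No baseline covariate is named, and nothing says that the arms share a baseline mean. Secondary outcomes follow the same strategy, with mixed linear models for continuous ones.

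The section Study outline and recruitment fixes the timing of baseline: "Study participation is commenced by an inclusion visit followed by a baseline period of at least 28 days". It continues: "At visit 2, prior to randomisation, a formal re-evaluation of study eligibility including a review of eDiary adherence and headache frequency, is performed".

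The Sample size section rests on the SD of a change: "The standard deviation (SD) for the change in number of headache days per week between baseline and week 5 – 8 was 7". The target is stated as "To detect a difference of 3.5 moderate to severe headache days per month between active and placebo groups in weeks 5 – 8". The planned power is 80% and the significance level 5%.

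**The concern.** With baseline as the reference period, the treatment main effect is the between-arm difference at baseline, and each interaction is a difference of changes. The baseline diary precedes randomisation, so any baseline difference is chance. The model nevertheless estimates it and then subtracts it in full from the treatment effect. Unless follow-up tracks baseline one for one, full subtraction is less efficient than regression on baseline, and the estimate stays correlated with whatever imbalance occurs. At stake is the width of the confidence interval for the single confirmatory comparison. Recruitment has ended (Study status), so the analysis is the main remaining place to gain precision.

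**Working it through.** **Structure of the model.** Two arms by four periods give 8 means. The stated terms use 1 (intercept) + 1 (treatment) + 3 (period) + 3 (interaction) = 8 parameters. The baseline means are therefore unconstrained. A common baseline mean would need 7.

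**Reproducing the sample size.** Inputs from Sample size and Study outline: SD of change 7, difference 3.5 days, 80% power, 5% level, 25% drop-out, 1:1 allocation. The level is taken as two-sided because the alternative hypothesis is that the arms differ. The SD is printed per week and the difference per month. I read both as days per four weeks, the only reading that reproduces the total.

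- Normal formula: n per arm = 2(1.96 + 0.84)² × 7² / 3.5² = 62.8, so 63; 126 / 0.75 = 168.
- t-test version: 64 per arm; 128 / 0.75 = 170.7.
- Stated total: 170, so it reproduces. Evaluable per arm: 170 × 0.75 / 2 = 63.75. The normal formula then gives 80.6% power.

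**Gain with equal variances.** The variance of the adjusted estimate over that of the change score is (1 − r²) / [2(1 − r)] = (1 + r)/2, and the residual SD is 7√[(1 + r)/2]. The values of r are assumptions.

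| r | Variance ratio | Residual SD | Total N needed | Power at 63.75 per arm |
|---|---|---|---|---|
| 0.3 | 0.65 | 5.64 | 110 | 93.8% |
| 0.5 | 0.75 | 6.06 | 128 | 90.3% |
| 0.7 | 0.85 | 6.45 | 144 | 86.5% |
| 0.9 | 0.95 | 6.82 | 160 | 82.5% |

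**Gain with unequal variances.** Let b be the slope of follow-up on baseline. Holding the SD of change at 7, the ratio is 1 − (1 − b)² × (baseline SD)² / 49. The gain vanishes at b = 1. Baseline SDs are assumptions.

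| Baseline SD | r | Follow-up SD | Slope b | Ratio | Power |
|---|---|---|---|---|---|
| 4 | 0.3 | 7.07 | 0.53 | 0.93 | 83.4% |
| 4 | 0.5 | 8.08 | 1.01 | 1.00 | 80.6% |
| 5 | 0.5 | 8.00 | 0.80 | 0.98 | 81.4% |
| 6 | 0.5 | 7.69 | 0.64 | 0.91 | 84.3% |
| 7 | 0.7 | 9.80 | 0.98 | 1.00 | 80.6% |

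**Chance imbalance.** Given a baseline difference of d days, the change-score estimate shifts by (b − 1)d. With equal variances and r = 0.5, b is 0.5 and the SD at each time is 7. A typical imbalance is then 7√(2/63.75) = 1.24 days, and the shift is about 0.62 days. Its share of the variance is 0.62² / 1.24² = 25%, the same saving as in the first table. This is the efficiency point seen another way.

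**Does the logistic model really behave like a change score?** The stated model was simulated with 64 per arm, four periods of 28 days and 600 runs per scenario. Three scenarios had an SD of change of 7.1 to 7.2. In the fourth the random-intercept model is exactly true.

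| r | Correlation of stated model's estimate (days) with raw change-score difference | Variance ratio, ANCOVA on counts / change score | Variance ratio (days), main effect dropped / stated model |
|---|---|---|---|
| 0.37 | 0.999 | 0.66 | 0.82 |
| 0.51 | 0.997 | 0.86 | 0.92 |
| 0.60 | 0.995 | 0.83 | 0.93 |
| 0.88 (model exactly true) | 0.977 | 0.96 | 0.96 |

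For the first three rows (1 + r)/2 gives 0.69, 0.76 and 0.80, so the simulated ANCOVA ratios are approximate. Removing only the main effect saves 4-18%, less than ANCOVA in the first three rows. A single shared intercept implies a very high correlation between periods (about 0.92 at an assumed daily intraclass correlation of 0.3), so baseline is still subtracted almost in full.

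These ratios compare true sampling variances. In the first three scenarios the stated model's own standard error was about half the true one. That is a separate matter of the covariance structure, but it bears on the fix.

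**The case against.** The endpoint, the hypotheses and the model target are all framed as change from baseline, and the trial was sized on the SD of change. Analysis and power calculation therefore agree, and relative to its own plan the trial loses nothing. This stands. A reader might infer that the trial is underpowered, or that subtracting baseline biases the result. Neither follows: the total reproduces, and the change-score comparison is unbiased under randomisation. The link to chance imbalance is a conditional property.

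It is also fair that 86-90% power is not an expected result. It requires equal variances and r between 0.5 and 0.7. Selection on headache frequency at entry, with a second review before randomisation, may narrow the baseline spread relative to follow-up, and that can push the gain towards zero. The evidence is indirect, because the entry criterion counts all headache days and not only moderate to severe ones.

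The last argument is that the article only summarises the model and defers to an SAP that is not shown. That SAP could indeed adjust for baseline. But the article names the treatment main effect explicitly, so the point concerns a stated term and not an omitted detail. If a common baseline was intended, as the restriction of the interaction to post-injection periods may hint, the listed main effect undoes it and the wording needs correcting.

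**Conclusion.** The point holds as an avoidable loss of precision, not as an error of validity. The stated model is in effect an unadjusted change-score analysis. Taking the SD of change as 7 days per four weeks, baseline adjustment would save between nothing (slope near 1) and 15-25% of the variance (equal variances, r 0.7 to 0.5), with about 35% at r 0.3. Power would correspondingly stay near 80% or rise to about 86-90%, and to about 94% at r 0.3. The document fixes neither r nor the variance ratio, so no single figure can be claimed. A reader might also infer that deleting the treatment main effect is enough. In the simulations that saved only about 4-18% on the days scale. The change is worth making but not essential.

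**What to change.** Before data lock, specify one of the following in the SAP:

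- Include each participant's baseline frequency of moderate-to-severe headache days as a covariate, with only post-injection days as outcomes.
- Keep baseline days as outcomes, remove the treatment main effect so that both arms share a baseline mean, and add participant-by-period random effects.

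In either case report the week 5-8 difference in days, averaged over participants. Because the arms have the same expected baseline, this estimates the same difference in mean change that the protocol targets. Apply the same choice to the mixed linear models for secondary outcomes. If the database is already locked, which the article does not say, keep the stated model as primary and report the adjusted one as a sensitivity analysis labelled as added later.

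No new data are needed and validity under randomisation is unaffected. The cost is a late change to a published primary model for a gain that may be small, so the date of the change and the fact that it was made blind to allocation should be recorded.

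### As described, the primary daily logistic model has no term for participants differing in how much they change; at the planning SD of 7 its standard error is about half the true value and the 5% test rejects about 30-37% of the time under no effect

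*Protocol article*

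**What the plan says.** The Primary efficacy endpoint section compares mean change between arms: "The treatment effect will be assessed by comparing the average change in the treatment group to that in the placebo group". The Research hypothesis is two-sided: the change "during weeks 5-8 post-injection differs between participants receiving onabotulinumtoxinA or placebo".

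The Sample size section works with each participant's change. It gives the SD of the "change in number of headache days per week between baseline and week 5 – 8 was 7" and plans "To detect a difference of 3.5 moderate to severe headache days per month", which "provided 80% power to reject the null hypothesis at 5% level nominal of significance", "assuming a drop-out rate of 25" per cent, for a total of 170. It also says that there is a single confirmatory hypothesis.

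The Statistical analysis section moves to the diary day. The dependent variable is binary for each recorded day from baseline to week 12. Treatment, four periods and treatment by post-injection period "are included as categorical fixed effects, and with participant ID as a random effect". Site will be assessed as a further random effect. The section is introduced as a brief account and refers to a SAP that is to be finalised before data lock. It names no participant-level variation in change, no within-participant correlation beyond the participant effect, and no robust variance.

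**The concern.** A participant random intercept absorbs differences in headache level. It does not absorb differences in change. Given the intercept, days are treated as independent, so two participants in the same arm with the same level are expected to change equally, apart from daily chance. In practice participants differ through placebo response, true response and natural fluctuation, and headache days cluster within attacks. The article itself expects differing response, since it defines 30%, 50%, 75% and 100% responders.

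The weeks 5-8 treatment-by-period term is the contrast on which this omitted variation acts. If the variation is present, the standard error is too small, the confidence interval too narrow and the p-value too low. The trial's only confirmatory claim rests on this term. The listed sensitivity analyses (technically successful bilateral injections, per-protocol set) restrict the population and would carry the same error.

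**Working it through.** **1. Reproduce the sample size.** Inputs from the Sample size section: difference 3.5, SD 7, power 80%, alpha 5%, two-sided by the Research hypothesis.

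n per arm = 2 x (1.96 + 0.8416)^2 x 7^2 / 3.5^2 = 2 x 7.849 x 4 = 62.8, so 63 per arm and 126 in total. With 25% dropout, 126 / 0.75 = 168, against 170 stated.

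The SD is labelled "The standard deviation (SD) for the change in number of headache days per week". On a weekly scale the difference would be 3.5 / 4 = 0.875, giving 2 x 7.849 x 49 / 0.766 = about 1,005 per arm. Also, a weekly count cannot change by more than 7 either way. The 7 must therefore be per 28 days, and it is used so below.

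**2. SD of change that the described model allows.** With daily headache probability p0 at baseline and p1 in weeks 5-8, the binomial variance of the change in a 28-day count is 28[p0(1-p0) + p1(1-p1)].

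- Upper bound, p0 = p1 = 0.5: 28 x 0.5 = 14, SD 3.74.
- p0 = 0.6, p1 = 0.5: 28 x (0.24 + 0.25) = 13.7, SD 3.70.
- p0 = p1 = 22/28: SD 3.1.

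The article gives no baseline frequency, so 14-22 days per 28 is an assumption. The upper bound does not depend on it.

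**3. Closed-form consequence.** Let r = (SD the model allows) / (true SD). The false-positive rate is 2[1 - Phi(1.96 r)]. At the upper bound of 3.74, where inflation is smallest:

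| True SD of change | r | 1.96 r | False-positive rate |
|---|---|---|---|
| 7 | 0.53 | 1.05 | 29.5% |
| 6 | 0.62 | 1.22 | 22% |
| 5 | 0.75 | 1.47 | 14% |
| 4.5 | 0.83 | 1.63 | 10% |

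With 22 baseline days (SD 3.1) and true SD 7, r = 0.44 and the rate is 39%. N cancels from r, so a larger trial does not help.

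**4. Simulation of the model as described.** No treatment effect; 64 per arm (170 x 0.75 = 127.5 in total); four 28-day periods; random-intercept logistic model fitted by maximum likelihood; Wald test of the weeks 5-8 interaction; 400 trials per scenario. Assumed: baseline mean 16 or 20 days, between-person SD 0.7 or 1.2 on the logit scale, and person-level change either shared across post-injection periods or independent by period.

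| SD of change | Model SE / true SE | False-positive rate |
|---|---|---|
| 7 | 0.47-0.50 | 31.5-37% |
| 6 | 0.52-0.63 | 22-32% |
| 5 | 0.63-0.72 | 15-23% |
| about 3.4 (no person-level variation in change) | 0.99-1.05 | about 5% |

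A separate simulation, with baseline about 17 days, gave 35% at SD 7.0, 25% at 5.9 and 17% at 4.45. Monte Carlo standard error is about 2.4 percentage points at a rate near 33%. The last table row shows that the model is sound when participants do not differ in change, so the omitted term causes the inflation.

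**5. Check of the remedy.** The same fit with participant-clustered variance rejected 3-6% of the time at SD 7 (3-7% over all scenarios). A t-test on each participant's change gave 4-6%. The version with an added participant-by-period random effect was not simulated.

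**The case against.** The strongest reply is that the article is a summary. Naming participant ID as a random effect identifies the grouping factor; it does not say intercept only, and it does not exclude robust variance. The unseen SAP may hold either. This stands as a limit: a reader might infer that the trial's confirmatory test is invalid, and the document does not support that. It supports the narrower statement that the model, as described, lacks what it needs. The article does list the outcome, the fixed effects and the random-effect candidates, and a random intercept is the natural reading of that list.

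The second reply concerns the SD of 7. It is mislabelled, and it comes from an open-label pilot of 10 participants, all actively treated. Under normality its 95% interval is 7 x sqrt(9/19.02) = 4.8 to 7 x sqrt(9/2.70) = 12.8, and part of the spread may be true drug response. This also stands. A single rate, such as one false positive in every three or four null trials, is too firm, so the result is given as a range by SD.

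Three further inferences fail:

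- That the effect will be reported only as a log odds ratio. The section states the aim as a difference in change in mean monthly headache days.
- That clustering of days within attacks makes matters worse than computed. With the SD of change held at 7, such clustering is already inside the 7.
- That the logistic model must give way to an ANCOVA or mixed model on 28-day counts. Those are valid, but choosing them is a preference. Nor is sizing on change scores and then fitting a mixed model wrong in itself.

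**Conclusion.** The point holds for the model as the article describes it. Its SD of change is capped at about 3.7 days per 28, while the sample size rests on 7. If 7 is right, the key standard error is about half its true value and the nominal 5% test rejects about 30-37% of the time under no effect. The rate is about 22-32% at SD 6 and about 10-23% at SD 4.5-5. It exceeds 5% whenever participants differ in how much they change.

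This rests on three assumptions: the random-intercept reading, an SD read as per 28 days, and assumed baseline frequency and between-person spread. The last moved the result little over the ranges tried. Because the single confirmatory test is affected, the matter must be settled before unblinding.

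**What to change.** In the SAP, before unblinding, do one of the following:

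- Add a participant-by-period random effect, or a random baseline-to-post change, to the logistic model.
- Keep the model and base the standard error, interval and test on participant-clustered robust or bootstrap variance.

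In either case report the treatment difference in change as days per 28 days with its 95% CI, and relabel the planning SD as per 28 days. If the SAP already contains one of these, correct the article's model description to match.

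The cost is SAP wording and model code; no new data are needed. The confidence interval will be wider, in line with the SD on which the sample size was based.
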